# Relapse after conservative surgery combined with triptorelin acetate versus conservative surgery only in women with focal adenomyosis: study protocol for a multicenter, prospective, randomized controlled trial

**DOI:** 10.1186/s13063-020-04294-2

**Published:** 2020-04-28

**Keywords:** Focal adenomyosis, Adenomyomectomy, Relapse, Triptorelin acetate

## Abstract

**Background:**

The preservation of fertility and integrity of the reproductive organs has increasingly been of concern to most women with adenomyosis. Adenomyomectomy is conservative surgery that is now widely applied; however, relapse is a serious problem after the operation. Postoperative treatment, such as gonadotropin-releasing hormone agonist (GnRHa) has been suggested to result in reducing the rate of disease recurrence. However, there is still a lack of evidence from randomized clinical trials examining the efficacy of GnRHa in decreasing the postoperative recurrence rate.

**Method/design:**

Relapse after conservative surgery combined with triptorelin acetate versus conservative surgery only in women with focal adenomyosis is a multicenter, prospective, randomized controlled trial. The primary outcome is relapse assessed using a visual analogue scale (VRS) and numeric rating scale (NRS), pictorial blood loss assessment chart (PBAC) score, and the size of the uterus and the lesion as measured by two/three-dimensional color doppler ultrasonography (2D/3D-CDUS) or magnetic resonance imaging (MRI). The secondary outcomes include quality of life, clinical pregnancy, ovarian reserve, adverse events, assessment by the Short Form (36) Health Survey and Female Sexual Function index, serum follicle-stimulating hormone, estradiol levels, and anti-Muellerian hormone and so on. All these indexes are measured at 3, 6, 12, 18, 24, 30, and 36 months after conservative surgery.

**Discussion:**

The result of this large, multicenter randomized trial will provide evidence for one of the strategies of long-term management in focal adenomyosis after conservative operation.

**Trial registration:**

Chinese Clinical Trial Registry: ChiCTR1800014340. Registered on 6 January 2018.

## Background

Adenomyosis is a common gynecologic benign disorder characterized by aberrant presence of endometrial glands and stromal cells within the myometrium [1–3]. The main symptoms are dysmenorrhea, chronic pelvic pain, dyspareunia, abnormal uterine bleeding (especially with heavy menstrual bleeding) and infertility, which seriously affect quality of life and work productivity in women of reproductive age [4, 5].

Hysterectomy is considered as radical therapy for patients who are refractory to other treatments or who do not wish to preserve their fertility [6, 7]. However, many patients of reproductive age are very concerned to preserve their fertility and reproductive organs [8]. Medical treatments or conservative surgery are options for these patients. The former include non-steroidal anti-inflammatory drugs or hormone regulating drugs, which can maintain a hypoestrogenic state, such as gonadotropin releasing hormone agonist (GnRHa), danazol, progestogens, or oral contraceptive pills [9, 10]. GnRHa has been the best acceptable treatment for patients during the past 20 years [11]. Unfortunately, these medicines may only provisionally improve symptoms and often lead to serious side effects [12]. Therefore, conservative surgery is an alternative; depending on the extent of the disease, the surgical options are adenomyomectomy (for localized adenomyosis) and partial adenomyomectomy (for diffuse adenomyosis) [4, 13]. The rate of pain relief after conservative surgery is higher in patients with focal adenomyosis than in those with diffuse adenomyosis [14]. However, discrepancy of relapse rate was the main issue for this treatment, due to the residual ratio of lesions. The cause was put down to the unclear cut line between focus and normal myometrial tissue [14]. How to control recurrence after surgery has become the current priority.

Recently, some prospective or retrospective studies [7, 15, 16] have confirmed that surgical-medical treatment is a more effective option for the treatment of symptomatic relief in focal adenomyosis than surgical treatment alone. However, there is still a lack of evidence from randomized controlled studies to confirm whether GnRH agonists could decrease the disease recurrence rate after conservative surgery in women with focal adenomyosis. This study is a multicenter, randomized, parallel controlled trial comparing the efficacy of triptorelin acetate in protecting against postoperative relapse in patients with focal adenomyosis.

## Method/design

Participants (*n* = 308) who have undergone complete excision of focal adenomyosis will be randomly assigned 1:1 to the treatment group (triptorelin acetate) or the control group. Patients will be recruited at 10 hospitals across mid-west China. All research units have been approved by the ethics committees. Every patient will sign an informed consent form prior to this study. This report follows the Standard Protocol Items: Recommendations for Interventional Trials (SPIRIT) guideline (Additional file 1).

### Inclusion criteria

The inclusion criteria are as follows:
Women aged ≥ 18 and ≤ 45 yearsWomen with pathologically confirmed diagnosis of focal adenomyosisWomen who accept complete excision of adenomyosis and have not taken any steroid hormone therapy in the 3 months before surgeryWomen who are healthy before and are not pregnantWomen who can comply with the study procedures and give written informed consent

### Exclusion criteria

Women who are also participating in other clinical trials at the same timeWomen who have concomitantly been diagnosed with ovarian endometrioma, deep infiltrating endometriosis, or multiple leiomyomasWomen with congenital uterine abnormalities such as uterine malformation (unicornis uterus, septate uterus, or duplex uterus) or acute genital inflammation or malignant tumorWomen who are pregnantWomen who have taken steroid hormone therapy in the 3 months before surgeryWomen with hereditary disease, blood disease, liver or kidney dysfunction, or malnutrition disorders that cause anemiaWomen, who may get contraindications, cannot tolerate surgery or are allergic to triptorelin acetateWomen who are unable to comply with the study procedures and give written informed consent

### Screening and enrollment

Previous medical history and current medication status are reviewed in the standardized case report forms. A physical examination and imaging such as two/three-dimensional color doppler ultrasonography (2D/3D-CDUS) or magnetic resonance imaging (MRI) are performed. Laboratory measurements include measurement of serum follicle-stimulating hormone (FSH), estradiol (E2), anti-Muellerian hormone (AMH), cancer antigen 125 (CA125), and safety assays including routine analysis of blood, urine, liver function, renal function, hepatitis virus, HIV, syphilis, and coagulation; electrocardiogram (ECG) and radiography are performed in the local departments at the study sites. Either laparoscopy or transabdominal surgery is performed to completely remove all clinically recognizable lesions in patients who are suspected to have focal adenomyosis.

Written informed consent will be obtained from the patients after surgery. Quality of life, degree of pain, and menstrual volume will be recorded using the Short Form (36) Health Survey (SF-36), Female Sexual Function Index (FSFI), pictorial blood loss assessment chart (PBAC) score, visual analogue scale (VAS) and numeric rating scale (NRS) after confirming by histologic assessment. A schedule of enrollment, interventions, and assessment is provided Table 1.

**Table 1 Tab1:** Schedule of screening, enrollment and assessment

Evaluation	Screening	Enrollment	Time of follow up after surgery (month)						
			3	6	12	18	24	30	36
Written consent		√							
Inclusion/exclusion criteria		√							
Medical history	√								
Physical exam	√								
Safety test (preoperative examination)	√								
2D/3D-CDUS/MRI	√		√	√	√	√	√	√	√
FSH, E_2_, AMH, CA125	√		√	√	√	√	√	√	√
Side effects			√	√	√	√	√	√	√
VAS and NRS		√	√	√	√	√	√	√	√
SF-36 and FSFI		√	√	√	√	√	√	√	√
PBAC score		√	√	√	√	√	√	√	√

*2D/3D-CDUS/MRI* two/three-dimensional color doppler ultrasonography/magnetic resonance imaging, *FSH* follicle stimulating hormone, *E*_*2*_ estradiol, *AMH* anti-Muellerian hormone, *CA125* cancer antigen 125, *VAS* visual analogue scale, *NRS* numeric rating scale, *SF-36* Short Form-36 Health Survey, *FSFI* Female Sexual Function index, *PBAC* pictorial blood loss assessment chart

### Adenomyomectomy

Laparotomy, hysteroscopy, or laparoscopy are performed in this study. During the laparoscopy, patients are in the lithotomy position under general anesthesia with endotracheal intubation. After sterilization, a pneumoperitoneum is created using carbon dioxide gas at 13 mmHg (Karl Storz GmbH & Co. KG, Tuttlingen, Germany). Surgery is performed using four surgical trocars. The supine position and a median incision are suitable for laparotomy. Hysteroscopic surgery is conducted for type 0 or type 1 adenomyoma (Karl Storz GmbH & Co. KG, Tuttlingen, Germany). The surgical approach is adenomyomectomy. The principles of these surgical options include complete removal of clinically visible lesions, maintaining the integrity of the uterine wall, and retaining the integrity of the uterine cavity as far as possible. The duration of surgery, size of the focus, blood loss, and the integrity of the uterine cavity should be recorded.

### Interventions

Eligible participants are assigned by simple randomization in a 1:1 ratio to a group receiving surgery only (group A) or to a group receiving surgery plus GnRH agonists (group B). The GnRH agonist is administered in the intervention group as a 3.75 mg intramuscular injection (Diphereline, Ipsen, France) on the first day of menstruation after surgery, then once every 4 weeks for six courses. The signs and symptoms of hypoestrogenism, including hot flushes, night sweats, sleep disorders, abnormal emotions and osteoporosis, could be caused by the GnRH agonist; these should be carefully evaluated and participants could be treated with tibolone 1.25 mg per day as add-back therapy to maintain serum estradiol at 30–50 pg/ml [17].

The intervention will be discontinued or modified if an intolerable adverse reaction occurs in group B. Color doppler ultrasonography and a steroid hormone test on the 3rd and 6th month after conservative surgery can help to monitor adherence. During the trial, other medications, such as steroid hormone or herbal medicine, or another intervention, such as levonorgestrel-releasing intrauterine system (LNG-IUS) will be prohibited.

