### Outcome and outcome assessments

The primary outcome is relapse, which is defined as recurrence of dysmenorrhea or pelvic pain, or menorrhagia, or local recurrence compared to the first follow up after surgery as confirmed by 2D/3D-CDUS/MRI. Relapse as identified by 2D/3D-CDUS or MRI constitutes an increase > 1 cm in the maximal diameter of the suspected recrudescent focus during the follow-up period. The VRS and NRS are also applied for evaluation of dysmenorrhea or pelvic pain and the recurrence is defined as any increase in the scores and by participants asking for other medical treatments for relief of symptoms at the same time during follow up. The PBAC score is used to predict coagulation disorders in women with menorrhagia and recurrence is defined as a score > 100. The proportion of participants with recurrence at 3, 6, 9,12, 18, 24, 30, and 36 months will be recorded.

The secondary outcomes include quality of life, clinically confirmed pregnancy, ovarian reserve, and adverse events (AE). Quality of life is assessed by the SF-36 and FSFI, as measures of health status and sexual functioning in women. Ovarian reserve is evaluated by measuring FSH, E_2_, and AMH; the first two are measured before surgery and during the follow-up period at the beginning of the menstrual cycle unless the participant is currently receiving treatment with triptorelin acetate. AMH can be measured at any time before and after surgery at the time of follow up. Differences in scores for eight dimensions (physical functioning, role-physical, bodily pain, general health, vitality, social functioning, role emotional and mental health) of the SF-36 and for the FSFI, and the mean values of FSH, E_2_, and AMH for will be recorded for assessment of quality of life and ovarian reserve participants in each group of participants at 3, 6, 9,12, 18, 24, 30, and 36 months. The participant’s intention to become pregnant, the pregnancy rate, and outcome are recorded in a standard case report form, including details of abortion, premature delivery, and full-term delivery, to evaluate differences in pregnancy outcomes in each treatment arm at 36 months.

The follow-up procedure is acquired from the outpatient department records. Follow-up visits occur at 3, 6, 12, 18, 24, 30, and 36 months after conservative surgery.

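### The ban on other treatment has no stated end at relapse, and treatment started between visits for recurrent symptoms is not by itself a relapse, so some treated women can be counted as relapse-free

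*Protocol article*

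**What the plan says.** Under Interventions, the protocol article states that throughout the trial "other medications, such as steroid hormone or herbal medicine, or another intervention, such as levonorgestrel-releasing intrauterine system (LNG-IUS) will be prohibited". No exception or end point is given for a woman who has relapsed.

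Under Outcome and outcome assessments, relapse can arise in three ways:

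- **Pain:** "any increase in the scores and by participants asking for other medical treatments for relief of symptoms at the same time during follow up". Both parts are needed. The Discussion repeats that recurrence of dysmenorrhea rests on the pain score together with a need to change treatment.
- **Bleeding:** on PBAC, "recurrence is defined as a score > 100".
- **Imaging:** relapse "constitutes an increase > 1 cm in the maximal diameter of the suspected recrudescent focus", judged against the first follow-up after surgery.

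On timing, "Follow-up visits occur at 3, 6, 12, 18, 24, 30, and 36 months after conservative surgery". On the source of the data, "The follow-up procedure is acquired from the outpatient department records". The Data analysis plan keeps women in the analysis by intention to treat and compares the 3-year recurrence rate with a Pearson chi-square test.

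The Background says of medical treatments, including hormonal ones, that "these medicines may only provisionally improve symptoms". It also says: "Hysterectomy is considered as radical therapy for patients who are refractory to other treatments".

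**The concern.** Two consequences follow if these rules are applied as written.

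First, the pain endpoint expects a woman to ask for other treatment, and the ban then denies her the hormonal, herbal and device options. Once relapse is recorded, her yes/no primary outcome is settled, and continuing to withhold treatment adds nothing to it.

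Second, if treatment is given before a criterion has been recorded, it can suppress the signs by which relapse would be recognised. Hormones or an LNG-IUS may lower pain and bleeding by the next visit. After hysterectomy, neither PBAC > 100 nor growth of a uterine focus can be recorded. Re-operation and hysterectomy are not named in the ban and are not relapse criteria either. Such a woman stays in the denominator and can enter the chi-square test as relapse-free, although her disease returned badly enough to be treated.

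At stake are avoidable untreated time for relapsed women and some real recurrences lost from the primary outcome.

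**Working it through.** **1. Which sequences count as relapse**

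| Sequence of events | Relapse as defined? |
|---|---|
| Pain score rises and the woman asks for treatment at the same time | Yes |
| PBAC > 100 recorded, then treated | Yes |
| Focus grows > 1 cm on imaging, then treated | Yes |
| Treated for pain between visits, no raised score recorded at that time | Not by treatment alone |
| Treated for bleeding before PBAC > 100 is recorded | Not by treatment alone |
| Re-operation or hysterectomy before any criterion is recorded | Not by treatment alone |

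The last three rows are the gap. Imaging or an entry in the outpatient record may still catch some of these women. After month 6 the scheduled visits are 6 months apart, which leaves room for treatment to start and take effect between them.

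**2. Longest wait under the ban** (visit times from Outcome and outcome assessments; end of follow-up at month 36)

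- Relapse recorded at the first visit, month 3: 36 − 3 = 33 months. This is the ceiling.
- Imaging relapse, which needs the month-3 visit as reference and so appears at month 6 at the earliest: 36 − 6 = 30 months.
- Relapse recorded at month 12: 36 − 12 = 24 months.
- Relapse first recorded at month 36: 0 months.

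**3. Women who could be affected by the ban** (rates of 49% and 28.1%, and 139 per arm, from Sample size calculation)

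- Group A: 139 × 0.49 = 68.1, about 68.
- Group B: 139 × 0.281 = 39.1, about 39.

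These are all expected relapses and therefore upper bounds. They include relapses first recorded at month 36 and imaging-only relapses that may need no treatment. If the first-year range in the Discussion (2.8–13.95%) is assumed to apply to group A, then 139 × 0.028 = 3.9 to 139 × 0.1395 = 19.4, or about 4 to 19 women, would relapse by month 12 and wait up to 24 months or more.

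**4. Effect of one misclassified woman**

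- Planned difference: 49 − 28.1 = 20.9 points.
- One woman: 100 / 139 = 0.72 points of her arm's rate.

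The document gives no basis for a count, so the 1 to 6 women below, all in one arm, are an assumption and not an estimate. Power is for the two-sided 5% test of two proportions with pooled variance under the null, at 139 per arm.

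| Relapses missed | Difference if all in group A | Power | Difference if all in group B | Power |
|---|---|---|---|---|
| 0 | 20.9 | 95.1% | 20.9 | 95.1% |
| 1 | 20.2 | 93.8% | 21.6 | 96.4% |
| 3 | 18.7 | 90.2% | 23.1 | 98.1% |
| 6 | 16.6 | 82.3% | 25.2 | 99.4% |

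Example: six missed in group A gives 20.9 − 6 × 0.7194 = 16.6 points.

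The power column starts at 95.1% and not at the stated 85% because 139 per arm does not reproduce from the stated inputs: the same formula at 85% power gives 96 per arm. That is a separate matter; 139 is taken here as the planned number.

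**The case against.** The case on the other side has five parts.

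- **Treatment does enter the pain definition.** A request for treatment is half of the criterion, and the other half is any rise in score, a very low threshold. A reader might infer that treatment for recurrence never counts as relapse. The text does not support that: most women treated for pain will have asked for treatment, and with a raised score they count. This stands, and it confines the point to treatment without a qualifying record.
- **Misclassification needs a chain of events.** The ban must be breached or surgery done, with no raised score, no growth > 1 cm and nothing caught in the clinic record. The definition speaks of follow-up generally, not only of scheduled visits. This also stands; nothing shows that such women will be numerous.
- **The ban may be meant to lapse at the endpoint, and a condensed article may leave that to the full protocol.** A reader might infer that relapsed women are in fact left untreated to month 36. The document does not say so. It does state an unqualified ban for the duration of the trial. That cannot be read as the six-injection period alone, because group A has no treatment period. The point concerns two stated rules, not a missing detail.
- **Counting treatment alone would let unblinded women and doctors create events.** This is correct, and it is the reason for not replacing the primary definition.
- **A ban to month 36 protects the longitudinal analyses.** Also correct; it is a real cost of lifting the ban.

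**Conclusion.** The point holds in limited form. As written, the ban does not end at relapse, although the pain criterion presupposes a request for the kind of treatment that is banned. Separately, started treatment is not itself a relapse, so a woman treated, re-operated or given a hysterectomy before a criterion is recorded can be counted as relapse-free.

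The wait is at most 33 months, and at most about 68 women in group A and 39 in group B could face one; both are ceilings. It would be wrong to conclude that the primary result is biased in a known direction. Missed relapses in group A shrink the difference, those in group B enlarge it, and the document shows neither their number nor their split. Only the unit effect, 0.72 points per woman at 139 per arm, is firm.

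It is unclear whether the ban also covers painkillers, and the conclusion does not depend on it. This is a cheap improvement that should be made, not a flaw that invalidates the design.

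**What to change.** **Interventions.** State that the ban ends once relapse has been recorded. Record the type, reason and start date of any prohibited treatment, re-operation or hysterectomy.

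**Outcome and outcome assessments; Data analysis plan.** Keep the stated relapse definition as primary. Before data lock, while the analysts are still blinded, pre-specify a supplementary 36-month chi-square comparison. In it, hormonal, herbal or device treatment, re-operation or hysterectomy for recurrent pain or bleeding counts as relapse on its start date. Report both results together.

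**Cost.** One wording change, one added record item and one added analysis; the primary definition is unchanged for women already enrolled. There are two downsides. Treatment decisions are made by women and doctors who know the allocation, so treatment-only events are open to bias; this is why the added comparison is supplementary. And treatment given after relapse will affect later pain scores, blood loss, lesion size, SF-36 and FSFI, so the GEE or MMRM results must be interpreted with that in mind.

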### Randomization

Eligible participants are assigned by simple randomization in a 1:1 ratio to one of two groups. The sequence of randomization has been set up by biostatisticians in the data coordination center using Microsoft Excel and the “RAND ()” function. The original sequence is safely kept by the staff in the data coordination center, and it has been put into the online central randomization system by these staff members, who are not involved in enrolling subjects. The sequence is not accessible to any investigators or study coordinators. If a subject fulfills the enrollment criteria, the authorized study coordinator will obtain the assignment for her. After randomization, both subjects and investigators are informed about the assignments.

### Outcome and outcome assessments

The primary outcome is relapse, which is defined as recurrence of dysmenorrhea or pelvic pain, or menorrhagia, or local recurrence compared to the first follow up after surgery as confirmed by 2D/3D-CDUS/MRI. Relapse as identified by 2D/3D-CDUS or MRI constitutes an increase > 1 cm in the maximal diameter of the suspected recrudescent focus during the follow-up period. The VRS and NRS are also applied for evaluation of dysmenorrhea or pelvic pain and the recurrence is defined as any increase in the scores and by participants asking for other medical treatments for relief of symptoms at the same time during follow up. The PBAC score is used to predict coagulation disorders in women with menorrhagia and recurrence is defined as a score > 100. The proportion of participants with recurrence at 3, 6, 9,12, 18, 24, 30, and 36 months will be recorded.

The secondary outcomes include quality of life, clinically confirmed pregnancy, ovarian reserve, and adverse events (AE). Quality of life is assessed by the SF-36 and FSFI, as measures of health status and sexual functioning in women. Ovarian reserve is evaluated by measuring FSH, E_2_, and AMH; the first two are measured before surgery and during the follow-up period at the beginning of the menstrual cycle unless the participant is currently receiving treatment with triptorelin acetate. AMH can be measured at any time before and after surgery at the time of follow up. Differences in scores for eight dimensions (physical functioning, role-physical, bodily pain, general health, vitality, social functioning, role emotional and mental health) of the SF-36 and for the FSFI, and the mean values of FSH, E_2_, and AMH for will be recorded for assessment of quality of life and ovarian reserve participants in each group of participants at 3, 6, 9,12, 18, 24, 30, and 36 months. The participant’s intention to become pregnant, the pregnancy rate, and outcome are recorded in a standard case report form, including details of abortion, premature delivery, and full-term delivery, to evaluate differences in pregnancy outcomes in each treatment arm at 36 months.

The follow-up procedure is acquired from the outpatient department records. Follow-up visits occur at 3, 6, 12, 18, 24, 30, and 36 months after conservative surgery.

Treatment-related AE are monitored at each visit. The AE are any unfavorable medical occurrences associated with the subject’s participation in the research, whether or not considered related to the study intervention. Serious adverse events (SAE) are events that are temporally associated with the subject’s participation in research that meet any of the following criteria: death, events that are life-threatening or severely or permanently disabling, events requiring in-patient hospitalization or prolongation of existing hospitalization, or any events deemed as serious by the local principal investigator. The proportion of patients with AE will be compared at 36 months to determine whether there is a difference between the groups.

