### Data analysis

#### Sample size calculation

Sample size was determined based on data from a prospective study demonstrating a relapse rate of about 49% in the group that received surgery alone and 28.1% in the group that received surgery and GnRH agonist treatment [7]. A two-tailed test with alpha set at 0.05 and 85% power is used to detect a minimum clinically meaningful difference between control and intervention groups. The minimal sample size is calculated as 139 participants in each group. In consideration of a dropout rate of 10%, we will recruit 308 participants in total.

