**Fig. 1 Fig1:**
[figure not shown]
Flowchart of this study

Intention to treat, which is based on the initial treatment intent, will be used as a foundation in our analysis. Participants who begin the allocated treatment are part of the trial, whether they finish it or not. The characteristics at baseline will be compared between the control and intervention groups. Continuous data will be summarized by the mean and standard deviation and the Wilcoxon rank sum test will be used to identify differences in baseline characteristic between the two groups. Categorical data will be described by number and percentage, using the Pearson chi-square test to compare data from the two groups.

The primary outcome measure is the difference in the recurrence rate between group A and group B after 3 years of follow up, which will be analyzed by the Pearson chi-square test. For efficacy parameters, such as the score for pelvic pain and dysmenorrhea, menstrual blood loss, and the size of the uterus and the lesion, will be analyzed using generalized estimating equations (GEE) or mixed effects model repeated measures (MMRM) to account for correlation among these observations at different follow-up points.

The variables from secondary outcomes, including scores on the SF-36 and the FSFI, the pregnancy rate, and pregnancy outcomes, are calculated during 36 months of follow up using GEE or MMRM analysis to compare groups A and B to identify differences between groups at different time points. The number of participants with adverse events (AE) or serious adverse events (SAE) will be calculated in each arm and taken into final statistical testing.

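### Ovarian reserve is stated as group mean AMH at each visit with no baseline adjustment, although pre-operative AMH is collected, so the comparison is less precise than it need be

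*Protocol article*

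**What the plan says.** In the protocol article, the section Outcome and outcome assessments names ovarian reserve as a secondary outcome and says how it is measured: "Ovarian reserve is evaluated by measuring FSH, E_2_, and AMH". The only summary given for it follows in the same section: "the mean values of FSH, E_2_, and AMH for will be recorded for assessment of quality of life and ovarian reserve", for each group at each follow-up time. That sentence speaks of differences in scores for the SF-36 and FSFI, but of means for the hormones.

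The Data analysis plan section assigns GEE or MMRM as follows: "The variables from secondary outcomes, including scores on the SF-36 and the FSFI, the pregnancy rate, and pregnancy outcomes". Ovarian reserve and its three hormones are not named there. No covariate is stated for any model. The one stated use of baseline data is a comparison of baseline characteristics between the groups.

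A pre-operative AMH value is planned for every woman. Table 1 ticks it at screening and at all seven follow-up visits, and the outcome section adds that "AMH can be measured at any time before and after surgery at the time of follow up". Randomisation follows surgery, so the screening value comes before allocation and is a valid covariate. Eligible women are aged 18 to 45, and allocation is by simple randomisation, without stratification by age or reserve.

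**The concern.** Preserving fertility is the article's own reason for conservative surgery, so whether six courses of a GnRH agonist leave ovarian reserve unchanged is a question readers will ask. If AMH differs between women at the start and part of that difference persists, a comparison of follow-up means leaves it in the error term. The screening sample could remove it. Without adjustment, confidence intervals for AMH at later visits would be wider than necessary, and a real difference would be missed more often.

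A chance difference in starting reserve would also pass in part into the follow-up comparison of the trial actually run. The stakes are modest: AMH is a secondary outcome, and the trial was not sized on it.

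**Working it through.** **The plan's own figure.** There is none for AMH: no SD, correlation, margin or power. The only sample size given is for relapse: "The minimal sample size is calculated as 139 participants in each group", from "a relapse rate of about 49% in the group that received surgery alone and 28.1% in the group that received surgery and GnRH agonist" treatment, two-sided 5% and 85% power. Those inputs do not give 139. With pooled variance:

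n = [1.96·√(2·0.3855·0.6145) + 1.036·√(0.49·0.51 + 0.281·0.719)]² / 0.209² ≈ 96 per group (106 with continuity correction).

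The figure 139 corresponds to about 95% power. That mismatch concerns the primary outcome and is a separate matter. Here 139 serves only as the number analysed per arm, which agrees with the recruitment target after 10% dropout: 308 × 0.9 / 2 = 138.6.

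**Assumptions, not in the documents.** The correlation ρ between pre-operative and follow-up AMH is taken as 0.3, 0.5 or 0.7. The true difference is 0.3 SD at one visit. The test is two-sided at 5%.

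**Formulas.** Adjustment for baseline multiplies the residual variance by 1 − ρ².

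- Power = Φ(0.3·√(139/2) / √(1 − ρ²) − 1.96), where 0.3·√69.5 = 2.501.
- Difference detectable with 80% power = 2.80·√(2(1 − ρ²)/139).
- Unadjusted number per arm giving the same precision = 139/(1 − ρ²).

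| ρ | Variance left | Power at 0.3 SD | Detectable difference (SD) | Equivalent unadjusted n per arm |
|---|---|---|---|---|
| 0 (unadjusted) | 100% | Φ(2.501 − 1.96) = 71% | 0.34 | 139 |
| 0.3 | 91% | Φ(2.622 − 1.96) = 75% | 0.32 | 153 |
| 0.5 | 75% | Φ(2.888 − 1.96) = 82% | 0.29 | 185 |
| 0.7 | 51% | Φ(3.502 − 1.96) = 94% | 0.24 | 273 |

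**Chance imbalance.** The standard error of a baseline difference is √(2/139) = 0.12 SD, so its 95% range is about ±0.24 SD. A fraction ρ carries into follow-up: about ±0.12 SD at ρ = 0.5. The unadjusted standard error already allows for this; adjustment removes it.

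**Why not a change score.** Its variance factor is 2(1 − ρ). Power at 0.3 SD is then 56%, 71% and 90% for ρ = 0.3, 0.5 and 0.7. That is worse than follow-up means below ρ = 0.5, and below the covariate model at all three values.

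**The case against.** The strongest objection is that the article prescribes nothing wrong. The outcome section says that means will be recorded; it names no test and does not call the comparison unadjusted. The list of secondary variables under GEE or MMRM is open, and since ovarian reserve is a secondary outcome, AMH may already fall under it. Covariates are commonly left to a full protocol or SAP, neither of which is shown.

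Much of this stands. A reader might infer that the plan fixes a raw test of AMH means, or excludes AMH from the repeated-measures analysis. The text supports neither. A reader might also infer that a chance baseline imbalance would bias the result towards a false drug effect. It would not: under 1:1 randomisation the unadjusted difference is unbiased, and its test keeps its error rate.

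What remains is narrower. The article does not merely stay silent. It gives visit means as the summary for ovarian reserve, names models for other secondary outcomes, and mentions no baseline adjustment. Reading AMH into the open list would give it a repeated-measures model, but that wording does not imply a baseline covariate.

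The size is also open to challenge. That differences in AMH between women persist through uterine surgery is an assumption, and the operation may lower ρ. At ρ = 0.3 the gain is only about 4 percentage points. The figures describe one visit adjusted for baseline alone, not the full multi-visit model with age.

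**Conclusion.** The point holds as an efficiency improvement, not as an error that invalidates a result. The stated ovarian-reserve measure makes no use of a pre-randomisation value that the schedule already collects. Under the assumptions above, adjustment would remove 9% to 49% of the variance and raise power for a 0.3 SD difference from 71% to 75–94%. The direction holds for any non-zero correlation; the size cannot be derived from the documents. The benefit of adding age is not counted in these figures. The point is minor: it affects precision for one secondary outcome and leaves the primary relapse test untouched.

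**What to change.** In Outcome and outcome assessments and in the Data analysis plan, state that AMH is compared between groups at the scheduled visits by the MMRM already named for secondary outcomes, preferably on log AMH, with pre-operative AMH and age as covariates. Keep the group means by visit as description. If an unshown SAP already does this, it is enough to bring the article's wording into line with it. The change should be settled before data lock.

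The cost is wording only, since AMH is scheduled at screening and age is needed for eligibility. There are two small downsides. Log-scale results are read as ratios of geometric means. A missing screening AMH needs a simple stated rule, such as imputing the overall baseline mean without regard to arm, so that no woman is dropped. How to treat values below the assay limit can be left to the SAP.
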